## Abstract

**Background:**

Lumbar spinal stenosis (LSS) causing neurogenic claudication is a leading cause of pain, disability and loss of independence in older adults. The prevalence of lumbar spinal stenosis is growing rapidly due to an aging population. The dominant limitation in LSS is walking ability. Postural, physical and psychosocial factors can impact symptoms and functional ability. LSS is the most common reason for spine surgery in older adults yet the vast majority of people with LSS receive non-surgical treatment. What constitutes effective non-surgical treatment is unknown. The purpose of this study is to evaluate the effectiveness of a multi-modal and self-management training program, known as the Boot Camp Program for LSS aimed at improving walking ability and other relevant patient-centred outcomes.

**Methods:**

We will use a pragmatic two-arm randomized controlled single blinded (assessor) study design. Eligible and consenting participants will be randomized to receive from licensed chiropractors either a 6-week (twice weekly) self-management training program (manual therapy, education, home exercises) with an instructional workbook and video and a pedometer or a single instructional session with an instructional workbook and video and pedometer. The main outcome measure will be the self-paced walking test measured at 6 months. We will also assess outcomes at 8 weeks and 3 and 12 months.

**Discussion:**

Symptoms and functional limitations in LSS are variable and influenced by changes in spinal alignment. Physical and psychological factors result in chronic disability for patients with LSS. The Boot Camp Program is a 6-week self-management training program aimed at the multi-faceted aspects of LSS and trains individuals to use self-management strategies. The goal is to provide life-long self-management strategies that maximize walking and overall functional abilities and quality of life.

**Trial registration:**

ClinicalTrials.gov ID: NCT02592642.

## Background

Lumbar spinal stenosis (LSS) refers to an anatomical narrowing of the central and/or lateral spinal canals [1]. It is usually caused by age related degenerative changes in the spine including intervertebral disc thinning, facet joint thickening and in-folding of the ligamentum flavum [2]. These changes contribute to a decrease in cross-sectional area of the spinal canal that can lead to compression and diminished blood flow to the spinal nerves [3, 4]. The clinical syndrome caused by LSS is known as neurogenic claudication. This syndrome is characterized by bilateral or unilateral buttock, lower extremity pain, heaviness, numbness, tingling or weakness, precipitated by walking and standing and [5] relieved by sitting and bending forward [2, 6]. Neurogenic claudication due to LSS is a leading cause of pain, disability and loss of independence in people over the age of 65 [7]. Limited walking ability is the dominant functional impairment caused by LSS [2]. Those afflicted have greater walking limitations than individuals with knee or hip osteoarthritis [8] and greater functional limitations than those with congestive heart failure, chronic obstructive lung disease or systemic lupus erythematosus [7]. Inability to walk among individuals with LSS leads to a sedentary lifestyle and a progressive decline in health status [9, 10]. Furthermore, symptomatic LSS is also associated with increased levels of depression; anxiety and hopelessness that can further perpetuate disability [11–14].

The prevalence and economic burden of LSS is growing exponentially due to the aging population. In Japan where 25 % of the population is over the age of 65, about 12 million people suffer from symptomatic LSS [15]. A similar epidemic is expected in the US by the year 2030 when an estimated 73 million people will be over the age of 65 [16] of which 30 % are projected to have symptomatic LSS [17]. LSS is the most common reason for spine surgery in individuals over the age of 65 [18], however only very few patients receive surgery [19]. The vast majority of individuals with LSS receive non-surgical care. However, what constitutes effective non-surgical care is unknown [20–23].

We have designed and implemented a training program for LSS known as the Boot Camp Program for LSS [24]. This program aims to address the multi-faceted aspects of LSS using a multi-modal non-surgical approach with a focus on self-management and the goals of improved walking ability, overall functional status and quality of life. The program considers the dynamic nature of LSS where symptoms change relative to posture. Reduction of the lumbar lordosis while standing, walking and sitting reduces epidural pressure and improves blood flows to spinal nerves [3, 11]. Enabling patients to introduce inter-segmental lumbar spine flexion (reducing the lumbar lordosis) using anterior pelvic tilt may reduce symptoms and improve walking ability [25–27]. Individuals with LSS tend to be deconditioned due to inability to walk and consequential sedentary lifestyle and may not have the necessary core strength and lumbar flexibility to accomplish this body realignment. They can also have reduced lower extremity strength due to combined nerve root compression and disuse. Specific flexibility, aerobic and core and lower extremity strengthening exercises, manual therapy and postural instruction may overcome these deficiencies.

The program also considers potential psychosocial consequences of LSS and incorporates a cognitive behavioral approach [28, 29]. This approach aims to improve coping and problem solving, build self-efficacy, provide feedback and develop realistic treatment and functional goals. Since LSS is a chronic and often-progressive condition [30] the program emphasizes incorporating learned physical and psychosocial self-management strategies for life. Patients receive an instructional workbook and video as part of the training program. The workbook and video provide education on self-management strategies and instruction on how to perform all the specific exercises and body realignment techniques. The workbook incorporates a schedule outlining the intensity and frequency of each exercise with goals tailored to each patient. The training program also includes a pedometer that provides weekly feedback for both patients and practitioners on walking ability.

In a previous retrospective study we evaluated 49 consecutive patients who completed the Boot Camp Program and assessed the difference in self-report outcomes selected a priori [24]. Outcome measures included the Oswestry Low Back Pain Disability Index, the walking score of the Oswestry Low Back Pain Disability Index, the three subscales of the Zurich Swiss Spinal Questionnaire, and the Numeric Rating Scale for leg and back pain. Following the 6-week intervention there were both statistically and clinically important improvements in all outcomes from baseline. This was a before and after study without a control group and therefore provided low quality preliminary evidence on the effectiveness of the program.

The purpose of this study is to assess the effectiveness of the Boot Camp Program in improving outcomes using a randomized controlled trial (RCT) design. Our main objective is to compare the effectiveness of a comprehensive 6-week self-management training program that includes a patient instructional workbook, video and pedometer to a single training session with provision of a patient workbook, video and pedometer. We hypothesize that the self-management training program will be more effective in improving walking capacity and functional outcomes than a single training session.

## Methods

### Design

We will conduct a pragmatic two arm single blinded (assessor) RCT (Fig. 1).

**Fig. 1 Fig1:**
[figure not shown]
Study Flow Process of f assessment

### Source population

Eligible participants are individuals who consult with specialists (orthopedists, neurosurgeons, rheumatologists, neurologists or physiatrists), family physicians or chiropractors for symptoms suggestive of neurogenic claudication at one of seven hospitals and several community clinics in Toronto, Canada and the surrounding area.

### Recruitment

Participating physicians and chiropractors will identify potential participants using an eligibility checklist (Table 1). Eligible potential participants will be given a pamphlet outlining information concerning the study and providing contact information for the trial coordinator. Interested and potentially eligible participants will be asked to contact the trial coordinator directly. Pamphlets will also be available in patient waiting rooms of participating hospital clinics and community clinics. Similar information will be advertised in local newspapers to enhance recruitment. The trial coordinator will provide details about the study and answer questions by phone. The coordinator will confirm eligibility including age, duration of symptoms and self-report walking ability. Walking ability will be assessed by the participants’ response to the question *“are you able to walk continuously for 30 min without the use of aids or without stopping to rest or stoop forward to alleviate your symptoms?*” Self-reported walking ability has been shown to be highly correlated (*r* = 0.80) to the self-paced walking test (SPWT) [31]. The SPWT is a validated objective measure of walking ability in LSS [31]. Only interested participants who respond “NO” and meet the other inclusion/exclusion criteria will be given an appointment for an intake assessment at the study site (Mount Sinai Hospital in Toronto Canada).

**Table 1 Tab1:** Inclusion and exclusion criteria

Inclusion criteria	
1. Age greater or equal to 50 years	
2. Clinical symptoms of back and/or radiating lower limb or buttock pain; fatigue or loss of sensation in the lower limbs aggravated by walking and/or standing and relieved by sitting.	
3. Intermittent or persistent pain without progressive neurological dysfunction	
4. Duration of symptoms and signs for more than 3 months	
5. Imaging confirmed spinal canal narrowing using MRI, CT scan, myelography or ultrasound	
6. Clinical signs and symptoms corresponding to segmental level of narrowing identified by imaging	
7. Patients with degenerative spondylolisthesis are included	
8. Not considered to be a surgical candidate (in the next 12 months) or patient unwilling to have surgery	
9. Able to perform mild-moderate exercise	
10. Able to walk without assistive devices for at least 20 m and less than 30 min continuously	
11. Able to give written informed consent and complete interviews and questionnaires in English.	
Exclusion criteria	
1. Severe degenerative stenosis with intractable pain and progressive neurological dysfunction	
2. Lumbar spinal stenosis not caused by degeneration	
3. Lumbar herniated disc diagnosed during the last 12 months	
4. Previous back surgery for lumbar spinal stenosis or instability	
5. Underlying spinal disorder such as ankylosing spondylitis, neoplasm, infection or metabolic disease	
6. Intermittent claudication due to vascular disease	
7. Severe osteoarthrosis or arthritis of lower extremities causing limited walking ability	
8. Neurologic disease causing impaired function of the lower limbs, including diabetes	
9. Psychiatric disorders and/or cognitively impaired	

### Inclusion and exclusion criteria

At the intake assessment, a licensed practitioner will assess potential participants. The assessment will confirm eligibility (Table 1) and will include a history, physical examination and a review of imaging results provided by the referring specialist. Eligible and willing participants will be asked to provide informed written consent. Consenting participants will be asked to complete a baseline questionnaire, a short physical performance battery (SPPB) [32] and perform a 30-min SPWT [31].

### Randomization to treatment groups

Randomization will take place following the completion of the consent process, baseline questionnaire, SPPB and the SPWT (Table 2). All participants will be randomly allocated to Group 1, the self-management training program with instructional workbook, video and pedometer or Group 2, a single instructional session and the instructional workbook, video and pedometer (Fig. 1). The randomization sequence will be prepared by the study biostatistician ahead of recruitment using a computerized random numbers table [NQuery Advisor® 7.0 [33]]. The biostatistician will provide the trial coordinator with sequentially numbered sealed opaque envelopes containing the allocation for Group 1 or 2. The study biostatistician will not be involved in the selection, treatment or follow-up of participants.

**Table 2 Tab2:** Measures collected at baseline and follow-up periods

Measures	Baseline	6 Weeks	3 Months	6 Months	12 Months
Socio-demographic characteristics	x				
Duration of symptoms (back or leg)	x				
Dominant pain (back or leg)	x				
Co-Morbidity Disease Index	x				
Self Paced Walking Test	x	x	x	x	x
Zurich Claudication Questionnaire (ZCQ) Symptom and Functional scales	x	x	x	x	x
Oswestry Disability index (ODI) and ODI walk	x	x	x	x	x
Numerical rating scale for back pain	x	x	x	x	x
Numerical rating scale for leg pain	x	x	x	x	x
36-item short-form health survey (V2)	x	x	x	x	x
Center for Epidemiological Studies-Depression Scale (CES-D)	x	x	x	x	x
Short Physical Performance Battery (SPPB)	x	x	x	x	x
Falls Efficacy Scale (FES)	x	x	x	x	x
Co-interventions and compliance		x	x	x	x

### Interventions and controls

Participants will be scheduled to begin either the self-management training program (Group 1) or the single instructional session (Group 2) based on their random assignment.

### Group 1: self management training program with instructional workbook, video and pedometer

Participants randomly assigned to Group 1 will receive the self management-training program with instructional workbook, video and pedometer at the study centre. All instruction and treatments will be provided by licensed chiropractors. Participants will be scheduled for twelve, 15-min sessions over a 6-week period (two treatment sessions per week). Four weeks following the 6-week treatment period a follow-up treatment (booster) session will be scheduled. Participants will be scheduled as regular patients at the Chiropractic Spine Clinic and Spinal Stenosis Program at Mount Sinai Hospital. All appointments will be confirmed 24 h in advance via telephone or e-mail as preferred by the participant as per usual treatment protocol. The intent is to provide participants with treatment that simulates real practice in terms of scheduling, time spent and content of treatment.

The Group 1 participants will receive the following:**Education:** Participants will receive instruction on self-management strategies using a cognitive behavioural approach [29]. Treating practitioners will provide information on the causes of pain and disability due to LSS, its natural history and prognosis. They will receive instruction on how to manage symptoms and maintain daily routines using problem solving, pacing, relaxation and body positioning [29, 34]. Reassurance, positive re-enforcement, goal setting and graded activity will be used to reduce pain related fear and improve self-efficacy [29, 35] and to improve function [36]. Participants will be instructed on how to reduce the lumbar lordosis when standing and walking using body repositioning techniques (the pelvic tilt).**Exercises:** Participants will receive instruction on muscle stretching, strengthening and conditioning exercises directed at improving overall back and lower extremity fitness and facilitating lumbar flexion [26, 37]. Tight muscles that promote lumbar extension (quadriceps, hip flexors, iliopsoas and erector spinae) will be progressively stretched and muscles that promote and control lumbar flexion will be strengthened (upper and lower abdominals). Exercise instruction will be provided and reviewed at each session and will be part of a progressive structured home exercise program. A graduated walking and/or stationary cycling program to improve lower extremity conditioning and overall fitness will be part of the home exercise program [38]. A written exercise and conditioning program schedule will be provided to participants outlining the type, frequency and intensity of the exercises to be performed. The exercises are to be performed twice per day at home with the number, intensity and frequency of each exercise increasing each week for a period of 6 weeks.**Manual Therapy:** The aim of the manual therapy will be to improve the flexibility of the lumbar spine and to facilitate lumbar inter-segmental flexion. At each session, manual therapy will be directed to the lumbar and thoracic spine, pelvis and lower extremities. Specific techniques will include low amplitude high velocity manipulation [26], joint, soft tissue, and neural mobilization [26, 39–41], lumbar flexion-distraction [27, 42], and manual muscle stretching [25]. The specific combination of manual therapy techniques used will be at the discretion of the treating practitioner based on identified underlying functional impairments.

Education, exercise instruction and manual therapy will be provided at each session and tailored to the needs of the participant by the treating chiropractor. An instructional workbook and video will be provided to all participants. This workbook and video provide education and a step-by-step guide on how to perform all the exercises and body realignment techniques, and are aimed at reinforcing the instructions received during the training sessions. The workbook also includes a diary to record exercise and self-management activities during the study period. Participants will also be provided a pedometer (Pedusa PE-771, Pedometers USA) with instruction and asked to record once per week the maximum number of continuous walking steps and time (minutes) to stop walking due to neurogenic symptoms.

### Group 2: single instructional session with instructional workbook, video and pedometer

Participants randomized to this group will receive the instructional workbook, video and pedometer provided and explained in a single 15–30 min session with a experienced licensed chiropractor not involved in the provision of the self-management training program. The emphasis on the instructional session is on reviewing the material in the workbook and the structure of the 6 week exercise program. No manual therapy will be provided during the session.

### Data collection and follow-up

Table 2 summarizes the data to be collected during the trial. We will follow-up with participants at 6 weeks, and 3, 6 and 12 months following randomization. A trained blinded assessor will conduct all follow-up assessments at the study site. Should patients be unable to attend a follow-up in person, all self-report measures will be administered via telephone. All assessors will receive training in order to standardize assessments and minimize inter- and intra-assessor variability. The assessors will be blinded to the treatment allocation and will be responsible for all follow-up assessment per assigned participant. The following outcomes will be measured at each follow-up.

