##### Co-interventions

We will measure co-interventions by asking participants to self-report the type and frequency of consultations with other health care providers and the type of interventions received beyond those provided in the trial. This would include physiotherapy, chiropractic, massage therapy, acupuncture, epidural injections and surgery. We will also ask participants if they have used medications and the frequency of use for their back and/or leg symptoms.

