##### Compliance

At each treatment visit and each follow-up assessment, we will ask participants about their compliance with their self-management programs (Groups 1 and 2). We will ask how often they are performing their exercises, body alignment techniques and self-management strategies. We will also assess compliance from the weekly exercise diary located in the instructional workbook.

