We have included a 1-month booster session following the 6-week training program. This emulates our current practice protocol at our Spinal Stenosis Clinic at Mount Sinai Hospital. The rationale being that LSS is a chronic condition and patients may benefit from periodic monitoring of their self-management skills and abilities. Periodic reassurance and positive reinforcement may also be of benefit especially among patients with underlying psychosocial barriers such as poor coping skills that accentuate functional limitations. Periodic monitoring and coaching may help to improve longer-term outcomes.

A leading cause of failure of RCTs is the lack of enrollment of sufficient number of participants into the study. We have enlisted a large referral source for potential participants. LSS is a very common condition seen by neurosurgeons and orthopedic spine surgeons, rheumatologists, physiatrists, family physicians and chiropractors. If our enrollment is deemed slow, we will expand our referral source to the University of Toronto vascular surgeons who also see a large number of patients with neurogenic claudication caused by LSS. We will also advertise in local newspapers and seniors publications. In addition, we will distribute pamphlets to be placed in-patient waiting areas at participating hospital clinics and in community clinics. Compliance to follow-ups may be problematic and we plan to provide incentives in the form of covering transportation costs up to $25 per day.

We anticipate that assessor blinding (to assigned intervention) during follow-up assessments will be challenging. We will implement strict rules preventing the communication, regarding participant allocation among participants, the research coordinator and blinded assessors.

Study design limitations include the lack of blinding of both practitioners and patients and this can introduce bias. The multi-modal and pragmatic nature of the design prohibits the determination of the component(s) of the intervention that may be responsible for potential improvements. There is potential for participants to receive other interventions during the intervention and between follow-up periods, which may impact the results. We will compare co-interventions receive between group and comment on the potential impact they may have on the results.

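### The blinded assessor's follow-up visits include compliance, co-intervention and, by inference, adverse-event questions whose answers can disclose the arm before the 6-month walking test

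*Protocol article*

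**What the plan says.** The protocol article describes a single-blind trial in which only the assessor is blinded; its Discussion lists the lack of blinding of participants and practitioners as a limitation.

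- **Who assesses.** Data collection and follow-up: "A trained blinded assessor will conduct all follow-up assessments at the study site". The assessors are blinded to allocation and each "will be responsible for all follow-up assessment per assigned participant".
- **What is assessed.** The same section ends "The following outcomes will be measured at each follow-up", and the list that follows includes Co-interventions and Compliance. Table 2 marks both at 6 weeks and at 3, 6 and 12 months.
- **Compliance.** "At each treatment visit and each follow-up assessment, we will ask participants about their compliance with their self-management programs (Groups 1 and 2". The content is the frequency of exercises, body alignment techniques and self-management strategies.
- **Co-interventions.** Participants report consultations with other providers and "the type of interventions received beyond those provided in the trial". Chiropractic is on the list of examples.
- **Adverse events.** They are assessed in both groups at each follow-up visit and are defined as unintended effects of the intervention. The section does not say who asks.
- **Safeguards.** The Discussion expects assessor blinding to be difficult and answers with a rule: "We will implement strict rules preventing the communication, regarding participant allocation among participants, the research coordinator and blinded assessors". Under Primary outcome, the assessor walks behind the participant without talking and records distance and time by instrument.

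**The concern.** The assessor is the only blinded party. The article nevertheless gives that person every follow-up assessment, and some of the items turn on what care the participant has had. Nothing in the article gives these items to someone else or places the walking test ahead of them.

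The arms differ in ways that are easy to mention. Group 1 has twelve sessions with manual therapy and then a booster. Group 2 has one session without manual therapy. A passing remark about sessions would be enough to identify the arm. Because the assessor stays with the participant, one remark at an early visit affects all later measurements by that assessor, including the primary endpoint. At stake is the credibility of the trial's only blinded measurements.

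**Working it through.** The document states no figure for this point, so the check compares sections.

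**1. Does the blinded assessor handle these items?** For compliance and co-interventions, yes on the article's wording: the assessor conducts all follow-up assessments, and both items are among the outcomes measured at each one. For adverse events it is an inference, because they are assessed at the follow-up visits but no person is named.

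**2. Can the answers disclose the arm?**
- *Compliance:* the items cover material that both arms receive through the workbook and video. A truthful answer fits either arm, so the risk lies in what a participant adds to it.
- *Co-interventions:* the question excludes trial care. To answer it on chiropractic, however, a participant has to separate trial sessions from other sessions. Someone with twelve sessions and someone with one may do this aloud in different ways.
- *Adverse events:* the listed symptoms also occur in the condition itself. The definition ties them to the intervention, so a participant may link a symptom to a particular treatment session.

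Disclosure is therefore possible under each heading, and no item asks for it directly.

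**3. Does an early disclosure reach the primary endpoint?** Yes. The first follow-up, at 6 weeks, falls at about the end of the 6-week programme. The booster comes four weeks after the programme, at about 6 + 4 = 10 weeks, before the 3-month visit. Both visits precede the 6-month endpoint and are made by the same assessor. (The Abstract gives the first follow-up as 8 weeks; the argument is the same.) Reordering the 6-month visit alone would therefore not be enough.

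**4. What could a knowing assessor influence?** In the SPWT, the judgement of a complete stop of 3 s, the stopwatch, and non-verbal cues. In the SPPB, the timing of the component tests.

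**5. Can the effect be sized?** No. The document gives neither a probability of disclosure nor a bias per disclosure. The following shows how far any figure depends on what is assumed. Suppose there is no true effect, 30 % respond in each arm (the article's Group 2 rate), and 42 per arm are evaluable (52 × 0.8 = 41.6). Let b be a spurious gain in Group 1. With p1 = 0.30 + b, p2 = 0.30, p̄ their mean, SE0 = √(2p̄(1 − p̄)/42) and SE1 = √((p1(1 − p1) + p2(1 − p2))/42), the probability of rejection is Φ((b − 1.96·SE0)/SE1) + Φ((−b − 1.96·SE0)/SE1).
- b = 0.025: SE0 = 0.1012, SE1 = 0.1011; result 5.7 %.
- b = 0.15: SE0 = 0.1056, SE1 = 0.1044; result 29.3 %.

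The answer runs from almost nominal to almost six times nominal according to a value of b that nothing in the document supports. No figure from this range is an estimate for this trial.

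**The case against.** The strongest reply is that the items are neutral between the arms and the protocol already guards the blind. Compliance questions concern content shared by both groups. Co-intervention questions steer participants away from trial care. The adverse-event section names no interviewer. The article admits the difficulty and sets a rule against communicating allocation. In the SPWT the assessor is silent, measures with instruments, and the participant decides when to stop. Visit order and form design are details that an article may leave to the full protocol, and co-interventions, described as self-reported, may already be on paper.

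Most of this is right, and it limits the point. A reader might infer that the answers necessarily give away the arm, that the questions contradict the rule on communication, or that blinding will probably fail by 6 months. The document supports none of these. The items do not ask about allocation, asking them does not breach the rule, and nothing allows the chance of failure to be estimated.

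What survives is narrower. The rule has to hold while the assessor's own visit raises topics that invite a slip, at up to three visits up to and including the primary one. Silence during the walk does not undo something learned earlier. The allocation of these items to the blinded assessor is the article's stated arrangement and not merely a missing detail.

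The unblinded participant's own effort is a separate route to bias. The article acknowledges the lack of participant blinding, and the change below would not affect this route.

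**Conclusion.** The point holds as an avoidable risk to assessor blinding. One assessor per participant conducts all follow-up assessments, and these include questions whose answers can, but need not, disclose the arm. A disclosure at 6 weeks or 3 months would carry over to the 6-month SPWT and to the SPPB. The stated safeguards lessen the risk without removing it.

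This rests on two readings: that all follow-up assessments includes the compliance and co-intervention items in the list that follows, and that adverse events assessed at the same visits are asked about by the same person. The second is inferred. The size of any bias is unknown, and no false-positive rate should be attached to it. The case for change is that the remedy is cheap and protects the only blinding the trial has.

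**What to change.** - At every follow-up, take the compliance, co-intervention and adverse-event questions away from the blinded assessor. Put them on a self-completed form that the participant returns sealed to the trial coordinator, who already handles the allocation envelopes.
- Do the SPWT and SPPB first at each visit.
- Record the assessor's guess of the arm at 6 months, so that the success of blinding can be reported.
- State in the adverse-events section who collects the follow-up reports. If the full protocol already separates these tasks, say so in the data collection section.

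**Cost.** One split form, a reordered visit and some coordinator handling: at the minimum sample size, at most 52 × 2 × 4 = 416 forms over the trial. The coordinator should open each form on receipt so that the existing reporting route for serious events is not slowed.
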